### Assessment of quality of life

Measurement of quality of life is one of the secondary objectives of the trial. Overall survival, return to previous employment as well as persistence of symptoms, the ability to perform appropriate activities and to care for oneself are criteria applied in the three questionnaires used in this study.

EORTC QLQ-C30 is a general measure of qualitiy of life in cancer patients. It incorporates nine multi-item scales: five functional scales (physical, role, cognitive, emotional, and social); three symptom scales (fatigue, pain, and nausea and vomiting); and a global health and quality-of-life scale [17]. Specific symptoms (dyspnoea, insomnia, anorexia, constipation, diarrhoea, and financial impact) are measured as six single items. This instrument has been used extensively with a variety of cancer patients and was able to discriminate between individuals with metastatic and non-metastatic disease, as well as between patients at different stages of illness. The scale has good internal consistency (alpha > 0.70), and good test re-test reliability (0.80 to 0.90) [18].

To assess disease-specific symptoms for patients with pancreatic cancer the pancreatic specific module (QLQ-PAN26) [19] that has been designed to use long with the general measure is used in this study.

The CES-D [20] is a 20-item self-report measure of depression that emphasises the emotional dimension. Its emphasis on the affective components of depression and is preferable for use in medical populations. It has demonstrated high internal consistency in both the general population and in patient populations and convergent validity with other measures of depression [21].

### Evaluation of the role of interferon alpha

In addition to the Virginia Mason and the MD Anderson study, an investigation of the effects and mechanism of INTRON A will be performed. IFN alpha seems to have the greatest activity of all interferons in malignancies [21-23] but its mode of action is poorly understood.

It probably consists of a combination of stimulation of cell-mediated cytotoxicity [24,25], direct antiproliferative anti-tumour activity, and an anti-angiogenic effect [15,26-31]. The known molecular and cellular effects of IFN-alpha appear to complement the mechanism of action of other therapies [28].

In view of the significant improvement in survival rates achieved by using interferon alpha in the Virginia Mason study, studies are now needed to define the molecular and immunologic mechanism(s) of this modality. If the mechanism of action of IFN-alpha is more clearly understood it can be applied more selectively and its therapeutic index will be enhanced.

Patients in study arm A at the CapRI trial will receive a single low-dose injection of 1 million units (LDI) prior to therapy. Accompanying immunological analysis should help to define predictive response markers. During therapy patients blood samples of approx. 20 ml will be drawn once a week for immunological studies. The panel will include immunophenotypings, detection of cytokine mRNA in lymphocytes, determination of cytokine patterns in peripheral blood, cellular cytotoxicity assays against autologous tumor cells and determination of apoptotic effects of interferon against autologous tumor cells.

### Statistical considerations and sample size estimation

The primary endpoint in this study is the overall survival period, measured from the date of resection. The sample size calculation is based on the assumption of a constant monthly hazard rate of 0.044 in the standard group and a constant monthly hazard rate of 0.021 in the experimental group. The hazard values are derived from two-year survival rates in the study groups (using the formula λ_group _= -1 × ln(P_24,group_)/24) with a two-year survival rate of 35% in the control group [11,12]and a conservative two-year survival rate of 60% in study arm A[13].

Assuming an accrual period of 18 months and a follow-up of 42 months [14,15], testing for a difference in hazard (hazard ratio ≠ 1) on level α = 0.05 and with a power of 80% a study sample size of 96 patients is needed. Taking into consideration the estimate of approximately 14 patients which will not complete the treatment, a total number of 110 patients should be randomised.

The overall survival will be summarised by Kaplan-Meier estimate and differences in therapy protocols will be analysed by univariate Cox-regression.

Various secondary endpoints will be evaluated in this study as well. Disease free survival, measured from date of operation, will be summarised by Kaplan-Meier estimate.

One year after inclusion of the first patient an interim analysis will be carried out which could result in stopping arm B. The planning of the study is based on a fix sample approach and not on groups sequential. Because the alpha level of the interim analysis is set to α = 0.001, the sample size calculated from a group sequential approach will be similar to the sample size of the fixed study approach.

The main evaluation will be performed two years after the last patient's enrolment.

There will be explicit stopping rules in place to terminate the trial early in the unlikely event that an unacceptably high rate of treatment related deaths (TRD) is observed. TRD will be monitored using the design of Thall and Simon [16]. A non-informative Beta prior distribution (i.e., B (0.015, 0.085) for TRD rate is assumed. The trial will be stopped if at any point during the trial there is a greater than 90% probability that the true TRD rate is greater than 0.05. Each patient will subsequently be evaluated and, an independent safety board will be consulted in making decision.

In view of the poor prognosis of the patient group, there will be no explicit stopping rules based on the overall number of toxicities, since even high rates of reversible toxicities seem acceptable if there is a large survival gain. Patients can withdraw from study participation at any time. Patients are taken off the study if unacceptable toxicity appears. Unacceptable toxicity is defined as unexpected serious side effects or irreversible Grade 4 toxicity. Patients who withdraw from the study may be treated with 5-FU and folinic acid or with gemcitabine. The decision will be based on the individual reasons for withdrawing from the study.

One year after inclusion of the first patient an interim analysis will be done. If at this time point there already is a significant difference between both groups favouring the Virginia Mason scheme (p < 0.001) group B (5-FU/Folinic acid) will be stopped and replaced by group C (chemoradiation without interferon alpha).

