### Study objectives

The primary objective is to compare the overall survival at two years postoperatively between two different methods of adjuvant treatment: therapy with 5-FU, cisplatin, interferon alpha 2b combined with radiation and the standard treatment from the ESPAC-1-Trial with 5-FU plus folinic acid.

Secondary objectives are to determine the role and the mechanism of interferon alpha 2b in patient's chemoradiation regimen, the toxicity, the disease-free interval and the quality of life. Different factors are tested in terms of their potential role as predictive markers.

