### Investigation schedule and follow-up

Pre-treatment evaluation for patients who are enrolled in study arm A includes a single low-dose (3 Mio U) injection of INTRON A prior to therapy (LDI). Blood will be drawn for intensive immunological studies. All patients (study arm A or B) must have appropriate lab and radiographic studies (CXR; CT abdomen [done post-operatively]; CBC; platelet count; BUN; creatinine; bilirubin, CA 19-9, and CEA) conducted prior to study enrolment to meet eligibility criteria.

During days 1–38 [study arm A] or during chemotherapy [study arm B] patients will be assessed with laboratory evaluation: complete blood count and blood chemistries weekly. Laboratory parameters in study arm A will be evaluated before each dose of cisplatin. Creatinine will be determined also one day after administration of cisplatin. Blood from members of study arm A will be investigated weekly for immunological markers.

Vital signs (blood pressure and pulse rate) and temperature are controlled daily during treatment. Patients are evaluated prior to receiving chemoradiation or chemotherapy. Patients enrolled in study arm A are evaluated weekly by the medical oncology and radiation oncology team during treatment. The team will check patients at each visit for symptoms due to therapy; a physical examination and complete safety labs should be performed. The patients' mental state will be investigated weekly. The questionnaire CES-D will be used as support. The three module questionnaire will be filled out during weeks 3 and 6 (study arm A) or week 3 and week 24 for study arm B.

During post-chemoradiation, infusional 5-FU (Study Arm A) patients will be evaluated by a physician prior to treatment and every 2 to 3 weeks with clinical assessment and laboratory parameters including a CBC, electrolytes, BUN, and creatinine. If patients undergo post chemoradiotherapy infusional 5-FU coordinated by an outside medical oncologist, a study nurse will contact the patient at least once weekly by telephone.

In the post-treatment period patients will be seen every 3 months by the surgical service for the first 2 years, every 4 months for the third year, and every 6 months during the 4th and 5th post-treatment years.

The aggregate clinical, laboratory, and imaging evaluations required per protocol as well as the timing of the optional three module questionnaire are outlined in table 1.

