The follow-up will be continued for two years. Follow-up data of overall survival will be evaluated annually.

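### Follow-up is described inconsistently: 96 patients match 80% power only if 42 months is the total study duration, and stopping each patient at two years would cut power below 80%

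*Protocol article*

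**What the plan says.** All places are in the protocol article.

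- **Statistical considerations and sample size estimation**, design inputs: "Assuming an accrual period of 18 months and a follow-up of 42 months". The test is two-sided at the 5% level, against a hazard ratio of 1. The requirement that follows is 96 patients for 80% power. Fourteen patients are added for those expected not to complete treatment, giving 110.
- **Same section**, timing of the analysis, counted from the final enrolment: "The main evaluation will be performed two years after the last". The Design paragraph of the abstract says the same of the primary endpoint.
- **Investigation schedule and follow-up**, visits: three-monthly for two years, then "every 4 months for the third year, and every 6 months during the 4th and 5th post-treatment years".
- **Same section**, next statement: "The follow-up will be continued for two years". Overall survival data are to be evaluated annually.
- **Study objectives**: "The primary objective is to compare the overall survival at two years postoperatively between two different methods of adjuvant treatment". The statistical section instead names the overall survival period from resection as the primary endpoint, to be analysed by Kaplan-Meier and univariate Cox regression.

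**The concern.** One primary endpoint is given several horizons. Eighteen months of accrual followed by 42 months of follow-up is 60 months. A main evaluation two years after the last enrolment is 42 months. A two-year follow-up period could mean 24 months for each patient, or 24 months after the last enrolment. The visit schedule runs to year 5, and the objective is worded as survival at two years.

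The design relies on deaths beyond month 24 in patients enrolled early. A site that closed survival follow-up at two years could point to the text in its defence, and those deaths would not be recorded. In an open-label trial it is also unwise to leave the censoring rule, and the choice between a fixed-time and an all-follow-up comparison, open to interpretation after data have accumulated.

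**Working it through.** **Inputs from the article.** Two-sided α = 0.05; power 80%; two-year survival 35% (control) and 60% (arm A); accrual 18 months. The control hazard is stated as "a constant monthly hazard rate of 0.044 in the standard group", and the experimental hazard as 0.021.

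**Assumptions not stated in the article.** 1:1 allocation, uniform accrual, no loss to survival follow-up, and enrolment treated as the start of survival time.

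**Step 1. Hazards, by the article's own formula.**
- Control: −ln(0.35)/24 = 0.04374
- Arm A: −ln(0.60)/24 = 0.02128
- Hazard ratio: 0.02128/0.04374 = 0.4866; ln(HR) = −0.7203

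**Step 2. Deaths needed (Schoenfeld).**
4 × (1.960 + 0.8416)² / 0.7203² = 60.5

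**Step 3. Probability of death.** With accrual a and minimum follow-up f:
p = 1 − exp(−λf) × [1 − exp(−λa)]/(λa)

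For a = 18 the bracketed ratio is 0.692 (control) and 0.831 (arm A).

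*Reproducing the article's figure: 42 months in total (f = 24)*
- Control: 1 − 0.350 × 0.692 = 0.758
- Arm A: 1 − 0.600 × 0.831 = 0.502
- Mean 0.630; N = 60.5/0.630 = **96.1**, matching the stated 96

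*42 months after accrual ends (f = 42, 60 months in total)*
- Control: 1 − 0.159 × 0.692 = 0.890
- Arm A: 1 − 0.409 × 0.831 = 0.660
- Mean 0.775; N = 60.5/0.775 = **78.1**

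*24 months for each patient*
- Control 0.65, arm A 0.40, mean 0.525; N = 60.5/0.525 = **115.2**

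**Step 4. Power** = Φ(½ × √deaths × 0.7203 − 1.960)

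| Follow-up | Patients | Expected deaths | Power | Range over formulas and hazard rounding |
|---|---|---|---|---|
| Common cut-off at 42 months | 96 | 60.4 | 80.0% | 77–82% |
| Common cut-off at 42 months | 110 | 69.3 | 85.0% | 82–87% |
| 18 + 42 months | 96 | 74.4 | 87.4% | 85–89% |
| 24 months per patient | 96 | 50.4 | 72.5% | 69–75% |
| 24 months per patient | 110 | 57.8 | 78.1% | 75–80% |

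The ranges cover the Schoenfeld, Freedman, Lachin-Foulkes and unpooled log-hazard-ratio formulas, each with rounded and unrounded hazards.

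**Step 5. Does the choice of formula change which reading fits 96?** Over the same variants the required N is 91–105 for 42 months in total, 74–85 for 18 + 42, and 110–125 for 24 months per patient. A further reading, 42 months for each patient, gives 80–92. Only the total-duration reading contains 96.

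**Step 6. Simulated log-rank tests**, 20,000 trials per scenario:

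| Scenario | Unrounded hazards | Rounded hazards |
|---|---|---|
| Common cut-off, 96 patients | 79.7% | 81.1% |
| 24 months per patient, 96 patients | 72.1% | 73.9% |
| 24 months per patient, 110 patients | 77.4% | 79.8% |

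**What the horizon costs in deaths.** With 96 patients, 60.4 − 50.4 = 10 expected deaths fall after month 24 and before the common cut-off.

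**The case against.** The strongest reply is that nothing has been miscalculated. The reading that reproduces 96 is also the one that fits the evaluation date, which is given twice. The two-year statement can be read in the same way, as two years after the last enrolment, and power is then 80%. The visits beyond year 2 mean that later deaths in early patients would probably be seen. The 14 added patients are non-completers of treatment, and stopping treatment does not remove a patient from a survival analysis. On that basis 110 is the fairer denominator, and even the least favourable horizon gives about 78%. The article is also a condensed account, and its schedule table is not shown.

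Most of this stands, and it limits the point in three ways.

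- A reader might infer that the sample size is wrong. The documents do not support that, because 96 follows from the stated survival rates and evaluation date.
- A reader might infer that the trial is powered at 72%, or that 80% holds under one horizon only. Neither follows. The 72% needs two conditions the article does not state: censoring each patient at month 24, and only 96 contributing. Power meets or exceeds 80% under both the 42-month and the 60-month readings.
- A reader might infer from the objective that the primary test compares two-year proportions and needs its own sample size. The statistical section plans no such test; it sizes on the hazard ratio and specifies Cox regression.

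What does not stand is the suggestion that this can be left to an unseen document. The article itself prints horizons that disagree, and the two statements in the follow-up section sit next to each other.

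**Conclusion.** The point holds as an inconsistency that bears on the stated power, of moderate severity. It is not an arithmetic error in N.

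Taken literally as follow-up after accrual, the stated input does not yield 96. The article's evaluation date shows that total duration is the likely meaning. The two-year follow-up statement conflicts with the visit schedule. If it is applied per patient, power drops by about 7 percentage points at either sample size: from 80% to about 72% with 96, and from about 85% to about 78% with 110.

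These figures rest on constant hazards at the planned values, 1:1 allocation, uniform accrual and no loss to survival follow-up. The figures for 110 also require that patients who stop treatment stay in the survival analysis.

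**What to change.** 1. **Statistical considerations and sample size estimation:** replace the 42-month follow-up phrase with *a total study duration of 42 months (18 months of accrual plus 24 months after the last enrolment)*.
2. **Investigation schedule and follow-up:** state that survival status is collected for every patient up to the common main evaluation date, and reconcile the two-year statement with the visit schedule that runs to year 5.
3. **Study objectives:** align the wording with the statistical section, with the hazard ratio over all follow-up as the primary comparison and two-year Kaplan-Meier survival as supportive.
4. **If 24 months per patient is really intended:** say so, and restate power as about 72% with 96 patients or about 78% with 110.

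The cost is wording in three sections. No patients are added and the evaluation date does not move. Survival status of early enrollees must be recorded past month 24, a period that the scheduled visits already cover.

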### Patient selection

CapRI focuses on hospitalised patients over 18 years of age treated with pancreatic head resection for pancreatic adenocarcinoma during an 18-month period started in August 2004. Men and women over eighteen years of age with biopsy-proven completely resected (R0 or R1) pancreatic adenocarcinoma of the pancreatic head or uncinate process will be screened for participation in the study. A detailed overview of all eligibility criteria is given in Table 2.

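### The primary survival comparison is fixed as an unadjusted Cox regression although margin status and CA 19-9 are known at baseline; prespecified adjustment would gain a little power at almost no cost

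*Protocol article*

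**What the plan says.** All references are to the protocol article.

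- **Endpoint and analysis** (Statistical considerations and sample size estimation): "The primary endpoint in this study is the overall survival period, measured from the date of resection". Survival is summarised by Kaplan-Meier, and "differences in therapy protocols will be analysed by univariate Cox-regression". No covariate, stratification term or supportive adjusted model for overall survival is named.
- **Margin status** (Patient selection): the trial screens patients with "biopsy-proven completely resected (R0 or R1) pancreatic adenocarcinoma", so margin status is mixed in the trial population and known at entry.
- **CA 19-9** (Investigation schedule and follow-up): the tests required of patients in both arms include "bilirubin, CA 19-9, and CEA) conducted prior to study enrolment".
- **Randomisation** (Randomisation and standardised treatment scheme): a computer-generated block list, with no stratification factor named.
- **Planning assumptions** (Statistical considerations): "constant monthly hazard rate of 0.044 in the standard group" and "constant monthly hazard rate of 0.021 in the experimental group", derived from planning "with a two-year survival rate of 35% in the control group" and "a conservative two-year survival rate of 60% in study arm A".

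**The concern.** As described, neither the randomisation nor the primary analysis uses baseline prognosis, although the Study design section calls the population heterogeneous and the Background section reports margin and nodal positivity when it describes a high-risk series. If margin status and CA 19-9 predict death, two things follow. A Cox model with treatment alone has less power than one that includes them. And in a trial of 110, a chance difference between the arms in either factor moves the estimated HR, with nothing in the planned analysis to take account of it. Because the article names the method, this questions a stated choice and does not ask for missing detail. At stake are some power and the precision of the result, not the validity of the test.

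**Working it through.** **1. The plan's own sample size**

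Inputs: two-year survival 35% and 60%, two-sided alpha 0.05, power 80%, 18 months' accrual, and main evaluation two years after the last enrolment (18 + 24 = 42 months in all). 1:1 allocation is assumed, because the ratio is not stated.

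- Hazards: -ln(0.35)/24 = 0.0437 and -ln(0.60)/24 = 0.0213, so HR = 0.487.
- Events (Schoenfeld): 4 × (1.960 + 0.842)² / (ln 0.487)² = 60.5, rounded up to 61.
- Probability of death by the analysis, with uniform accrual over A = 18 and minimum follow-up F = 24: 1 - [exp(-λF) - exp(-λ(A+F))]/(λA). This gives 0.758 in control and 0.502 in arm A, mean 0.630.
- Patients: 61/0.630 = 96.9, or 97, against the stated 96.

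The stated size therefore reproduces as an unadjusted calculation on group-level survival. The HR of 0.487 is a marginal one.

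**2. Chance imbalance in margin status**

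The only R1 share in the document is 19%, from the external phase II series of 43 patients (Background). With 55 per arm, the SD of the difference is √(2 × 0.19 × 0.81/55) = 7.5 points. A gap of 10 points or more means at least 6 patients, and the exact binomial probability is 0.180. If the R1 share were 30% (assumption), it would be 0.25.

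**3. What an imbalance would do to the unadjusted HR**

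The approximate shift is (factor HR) raised to the size of the gap. Factor HRs are assumptions.

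- An R1 gap of 15 points, about the 95% limit at 19% R1: 1.5^0.15 = 1.06; 2.0^0.15 = 1.11.
- A CA 19-9 gap at its 95% limit, 1.96 × √(2/55) = 0.37 SD: 1.3^0.37 = 1.10; 1.5^0.37 = 1.16.

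**4. Power with and without adjustment**

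The document gives no prognostic strengths, so a range is assumed. The simulation used 2,000 trials per row, 30% R1 and standardised log CA 19-9, with the marginal two-year survival held at the plan's 35% and 60%.

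| HR for R1 / HR per SD of CA 19-9 | Conditional treatment HR | N=110 unadjusted | N=110 adjusted | N=96 unadjusted | N=96 adjusted |
|---|---|---|---|---|---|
| 1.0 / 1.0 | 0.487 | 0.834 | 0.831 | 0.787 | 0.778 |
| 1.3 / 1.2 | 0.480 | 0.833 | 0.841 | 0.789 | 0.802 |
| 1.5 / 1.3 | 0.473 | 0.835 | 0.860 | 0.778 | 0.815 |
| 1.5 / 1.5 | 0.461 | 0.836 | 0.882 | 0.794 | 0.842 |
| 2.0 / 1.5 | 0.451 | 0.835 | 0.895 | 0.766 | 0.843 |

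The simulation standard error of one power figure is about √(0.834 × 0.166/2000) = 0.8 points, so the smallest gain is close to noise. With 19% R1 and HRs of 1.5 and 1.3, power at 110 was 0.839 unadjusted and 0.856 adjusted.

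The gain in patients is 110 × [((1.96 + z_adj)/(1.96 + z_unadj))² - 1], where z is the normal quantile of the power. The weakest prognostic row gives about 2 patients and the strongest about 22.

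**5. Type I error**

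With no treatment effect, rejection rates were 0.0475 (unadjusted) and 0.048 (adjusted) for HRs 1.5/1.3, and 0.044 and 0.055 for 2.0/1.5. Both models hold the level to within simulation error.

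**The case against.** The strongest reply is that nothing here is wrong. After randomisation an unadjusted Cox comparison is valid, chance imbalance is already covered by its type I error, and the sample size matches the planned analysis. All of that stands.

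Three stronger readings are tempting, and the document supports none of them.

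- **That the trial is underpowered without adjustment.** If 0.487 is taken as the conditional HR, with R1 at HR 2 and CA 19-9 at 1.5 per SD, unadjusted power at 110 falls to about 76%. But the plan derives its hazards from group survival, so 0.487 is marginal. With 35% and 60% held, unadjusted power stays at about 83%. At 96 patients the simulated unadjusted power is 77% to 79%, but the document says that the 14 extra patients are expected not to complete treatment, not that they leave the survival analysis.
- **That the unadjusted HR is biased towards 1.** The unadjusted HR lies nearer to 1 than the conditional one because hazard ratios are non-collapsible. It estimates the marginal effect on which the trial was sized.
- **That nodal status and post-operative CA 19-9 are on hand.** Nodal status is not listed as collected. In the pre-enrolment tests only the abdominal CT is marked as post-operative; CA 19-9 is required only before enrolment.

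It is also fair that an analysis plan not shown here may add a supportive adjusted model. That would not change the primary analysis, which the article itself fixes as univariate. Finally, the gain rests on assumed prognostic strengths, and at the low end it is negligible.

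**Conclusion.** The point holds as a modest, nearly free improvement. The stated primary analysis leaves out two baseline variables that the trial already has in both arms. At 110 patients, and with the plan's own two-year survival rates, prespecified adjustment adds about 1 to 6 points of power to a base of about 83%. This assumes an HR of 1.3 to 2.0 for R1, 1.2 to 1.5 per SD for CA 19-9, and 30% R1. If neither factor is prognostic there is essentially no gain and no material loss. An R1 gap of 10 points or more has an 18% chance if the share is the external series' 19%. A reader should not infer that the planned test is invalid, or that the trial misses its 80% target because of it.

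**What to change.** In Statistical considerations and sample size estimation, replace the univariate model with a Cox model for overall survival containing treatment, margin status (R0/R1) and log pre-enrolment CA 19-9. Fix the covariates and their coding before the interim analysis: the trial is open, and covariates chosen after data have been seen would not be credible. Report the unadjusted HR and the Kaplan-Meier curves as supportive. Add nodal status only if it is recorded for all patients.

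The cost is one sentence. No patients and, for these two covariates, no extra tests are needed. The downside is one of interpretation: the adjusted HR is conditional on the covariates, tends to lie further from 1, and is not the marginal HR behind the sample size. The report should say so and show both.

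### Stopping treatment is handled as leaving the study, although the endpoint is overall survival: this risks toxicity-dependent loss, and the 96-to-110 allowance does not cover dilution if everyone is analysed

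*Protocol article*

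**What the plan says.** All the relevant statements are in the section on statistical considerations and sample size estimation of the protocol article.

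- **Endpoint:** "The primary endpoint in this study is the overall survival period, measured from the date of resection". The main test is a univariate Cox regression.
- **Sample size:** 96 patients give 80% power at a level of 0.05. The section then adds: "Taking into consideration the estimate of approximately 14 patients which will not complete the treatment, a total number of 110 patients should be randomised". The allowance is for not completing treatment, not for loss to follow-up.
- **Toxicity:** "Patients are taken off the study if unacceptable toxicity appears". The sentence refers to the study, not to the study treatment.
- **Later therapy:** "Patients who withdraw from the study may be treated with 5-FU and folinic acid or with gemcitabine". The first option is the arm B regimen.

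The section on study design describes the trial as open.

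**The concern.** A patient who stops treatment can still be followed to death or to the data cut-off. The article's wording and its sample size arithmetic both point the other way: the patient leaves the study, and 110 randomised are counted as 96 who supply data.

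Two different problems follow, depending on what is done.

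1. **Patients are lost to follow-up or censored at removal.** Removal is driven by toxicity, and toxicity may go with frailty and poor prognosis. Removal is also decided with the arm known. If one arm loses more such patients, the remaining comparison is no longer the randomised one, and that arm looks better than it is. A later analysis plan cannot recover deaths that were never collected.
2. **All 110 are analysed as randomised.** This is the sound analysis, but arm A patients who stop early and move to the control drugs may lose part of the assumed benefit. Adding 14 patients for 14 lost covers missing data. It was not derived for a diluted effect.

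**Working it through.** **Inputs from the article.** The article gives "a two-year survival rate of 35% in the control group" and "a conservative two-year survival rate of 60% in study arm A", an accrual of 18 months, a main analysis two years after the last enrolment, a two-sided level of 0.05 and power of 80%. Equal allocation is assumed, since the ratio is not given.

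**Step 1: reproduce 96 and 110.**
- Hazards: λ = -ln(S)/24. Control: -ln(0.35)/24 = 0.04374. Arm A: -ln(0.60)/24 = 0.02128. These agree with the article's 0.044 and 0.021 after rounding. HR = 0.02128/0.04374 = 0.487.
- Events (Schoenfeld): 4 × (1.960 + 0.842)² / (ln 0.487)² = 60.5, rounded up to 61.
- Probability of death by the analysis: 1 - [exp(-24λ) - exp(-42λ)]/(18λ) = 0.758 (control) and 0.502 (arm A), mean 0.630. This takes the stated 42 months as total duration, 18 + 24.
- N = 60.5/0.630 = 96 (61/0.630 = 96.9 with events rounded up). Power at 96 is 0.800.
- Allowance: 14/110 = 12.7%, and 96/(1 - 14/110) = 110.

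The plan's figures therefore reproduce. The last line shows that the 14 are counted as giving no survival data.

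**Step 2: power with all 110 analysed as randomised.** Log-rank tests were simulated with 55 per arm, uniform accrual over 18 months and analysis at 42 months. A number k of arm A patients lose all or half of the benefit from the start. The value of k and the size of the loss are assumptions.

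| k of 55 in arm A | Control hazard (full loss) | Half the benefit lost |
|---|---|---|
| 0 | 84-85% | 84-85% |
| 3 | about 80% | – |
| 4 | 79% | – |
| 7 (even split of the 14) | 73-75% | 79-80% |
| 10 | 69% | 78% |
| 14 (all in arm A) | 60-62% | 73-74% |

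The ranges reflect simulation error and, for half loss, whether the half is taken on the hazard or on the log hazard ratio. For comparison, an inflation for full dilution in 12.7% of arm A would be 96/(1 - 0.127)² = 126, not 110.

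**Step 3: bias if removed patients are lost.** These runs have no true effect, and all their inputs other than the total of 14 are assumptions.
- Censoring at removal: 25% of patients are frail with 3 times the hazard and are 5 times as likely to be removed, with 12 removals in arm A and 2 in arm B. The false-positive rate favouring arm A is 4-5%, against about 2.5% with full follow-up. In the run that estimated it, the mean HR was 0.94.
- Dropping patients outright: 7 to 14 arm A patients with 1.5 to 2 times the hazard are left out. Two-sided type I error is 0.057 to 0.10.
- With equal removal in both arms, symmetry implies no shift towards either arm in the censoring case. The bias needs unequal removal as well as a link with prognosis.

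**The case against.** The strongest reply is that the harmful analysis is nowhere stated. The article does not say that removed patients are left out of the Cox model, censored at removal or lost to follow-up. The section on investigation schedule and follow-up has overall survival evaluated annually, with no exception for them. Intention to treat is in the abbreviation list, together with other terms the shown text does not use, which suggests a fuller document that may settle the matter. This stands as far as it goes: exclusion is the natural reading, not a stated rule, and the lack of a named analysis set in an article is not the point here. What remains is what the article does state: removal from the study for toxicity, and a sample size that counts non-completers as absent.

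A reader might go further in three ways that the documents do not support.
- **That non-completers are replaced one by one.** They are not; 14 are added in advance.
- **That analysing all 110 must give less than 80% power.** It gives about 84% if non-completers keep the full effect, and about 80% if 7 lose half of it. The assumed 60% is called conservative and is close to the 64% that the Background section reports for the phase II series. If that rate already includes non-completers, some dilution is already in the design hazard. Patients who stop late, or who receive gemcitabine, may also lose less than assumed.
- **That the 14 is too small because more deaths than that could occur during treatment.** Deaths are endpoint events already counted in the 96 and need no allowance.

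**Conclusion.** The point holds in conditional form. The article handles the end of treatment as a loss of survival data in two places, and neither suits an overall survival endpoint.

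The size depends on facts the documents do not give: the arm split of the 14, their prognosis, and how much benefit they lose. Under the stated frailty assumptions the inflation of false positives is moderate, from about 2.5% to 4-5% in favour of arm A. With everyone analysed, power lies between about 61% and 84%. It stays at 80% or above only while no more than 3 or 4 arm A patients have the control hazard, or about 7 lose half the benefit. No single figure, 80% or 74%, can be quoted without its assumption. The correction still matters because follow-up that is not collected cannot be restored at the analysis.

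**What to change.** 1. Reword the toxicity sentence so that protocol treatment ends while the patient stays in the study. Follow every randomised patient for survival unless consent to follow-up is withdrawn. Keep withdrawal from treatment and withdrawal of consent as separate categories.
2. State that the primary Cox analysis includes all 110 randomised patients by allocated arm, censored only at the date last known alive. Any analysis of completers is a sensitivity analysis.
3. Say whether the 14 stand for missing survival data or for diluted effect. Present the 80% as conditional, and give the range of about 61-84% with the dilution assumption behind each value.

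No change is proposed to when treatment ends or to what patients receive afterwards. The cost is a few sentences of protocol text, survival follow-up contacts for about 14 patients, and a less favourable but defensible power statement. A larger sample is not required by this point.
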